### Group A: stuck-moving needle acupuncture MTrp treatment group

#### Selection and positioning method of shoulder joint myofascial trigger pain points

The selection of shoulder joint myofascial trigger pain points will be achieved by a dynamic search. Further, patients will be subjected to do three actions including the first one as abduction, lifting, and touching the head. The second one is forward flexion and internal rotation by touching the opposite shoulder. The third one is a posterior extension and touching patient’s back. These three actions can indicate the patient’s pain area. At the same time, the doctor will use his or her thumb to press these areas and confirms the muscle tension band. The compression can lead to localized pain and muscle spasm and strengthen the stimulation to induce the mentioned pain. Once the pain is induced, the doctor will ask the patient if the pain is similar to what he or she usually feels. If the pain is similar to the pain patient usually feels, then the doctor will place a pressure manometer on the main tenderness point to evaluate the pain point. Further, by placing the pressure manometer (Wagner Instruments, USA, specification model: FDK20) at the pain area, slowly pressure will be applied. Using this equipment, doctor can measure the tenderness threshold and can remove the pain points below the tenderness threshold of 2 kg/cm^2^. After locating the pain points, the doctor will use a black pen to draw “×” on it.

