#### The stuck-moving needle acupuncture method

The patient will take a seated position during acupuncture. After routine disinfection on the selected myofascial trigger points (MTrp), the skin will be cleaned with alcohol (75%). The applicator will tighten the patient’s skin with his or her left hand and will hold the stuck-moving needle (specification, 0.40 × 40 mm) in his or her right hand (the position of the needle is approximately 1 cm from the needle tip), and the stuck-moving needle will be inserted perpendicularly into the Trp (the degree of convulsions after the patient’s pain is triggered). Further, a needle will be twisted clockwise slowly (90–180°) until the muscle fibers are wounded and until the needle becomes tight and twisted. At this point, patient may describe pain and astringency. Then, the needle will be lifted again with 3 to 5 times by shaking. The strength of lifting the needle will depend on the patient’s condition and acupuncture position. Furthermore, a needle should be ejected quickly. While lifting the needle, the doctor will twist needle counter clockwise until the muscle fibers are relaxed. After the treatment, the patient will be supplemented with physical exercises. The exercise method is same as provided to group C.

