### Secondary outcome

#### Measurement of pressure pain threshold (PPT) and pressure pain tolerance (PTT)

This study will be performed using the FDK20 handheld pressure an algeometer manufactured by Wagner Instruments, USA. The device measures the individual’s pain sensitivity by applying pressure which includes measuring the pressure pain threshold (PPT) and the pressure pain tolerance (PTT). Initially, the data that will be transferred to the tester when the subject just felt pain, which will be recorded as PPT. Furthermore, after a short pause, the pressure will be increased until the pain becomes intolerable to the subject. After a short pause, the tester may increase the pressure until the patient feels that the pain caused by this pressure is intolerable. When the patient informs the tester for the second time, the tester will record it as PTT. The test value of the pain indicator is only visible to the tester during the whole process. The tester sequentially measures the pain threshold and pain tolerance threshold of the patient’s marked points, and the test interval for different points is 5 min. The data will be analyzed in units of kg/cm^2^.

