The needle application site is a key factor that affects the effect of acupuncture. In this study, the operation site of the stuck-moving needle is the localized MTrp of the shoulder joint. Studies in recent years have found that the occurrence of frozen shoulders is often related to the muscles around the shoulder joint related to the pain points [34, 35]. These muscles include deltoid muscle, biceps, pectoralis major, pectoralis minor, and coracobrachialis muscle. These points of muscle are common, and it can cause pain and impair shoulder movement. If it can be accurately positioned in clinical treatment for effective treatment, the effect will be greatly improved. The pain points of the affected muscles of the shoulder joint are characterized by tenderness, which restricts the complete extension of the muscles, causing muscle weakness, and can be directly compressed to conduct the patient’s identifiable pain, whereas sufficient stimulation can cause twitch response. Based on the characteristics of MTrp with tenderness and referred pain [36], we used a pain meter to determine the location of the local pain points in the shoulder joint and then performed a stuck-moving needle operation with a marker to ensure the accuracy of the operation. During this study, we used patented stuck-moving needles termed as Li Zhenquan’s needles, produced by Suzhou Acupuncture Supplies Co., Ltd., with a size of 0.4 × 40 mm.

The stuck-moving needle acupuncture method can increase the stimulation intensity, breadth, and depth of acupuncture. It is applied to the Trp for the localized activation of the shoulder joint, making the local capillaries of the Trp quickly contract and relax, improve the state of local tissue microcirculation, and accelerate the local metabolism. At the same time, by increasing the intensity of acupuncture, it can increase the rapid release of certain analgesics in the pain point. This relieves pain symptoms.

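### As written, the 2 kg/cm² rule for choosing group A needling points drops what are probably the most tender candidates; its direction needs correcting or explaining

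*Protocol article*

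**What the plan says.** In the Group A part of the protocol article, under the selection and positioning of trigger pain points, candidates are found in stages. Three shoulder movements show the painful area. The doctor then presses with the thumb to confirm a taut band and asks whether the provoked pain is the familiar one. The gauge comes next: "If the pain is similar to the pain patient usually feels, then the doctor will place a pressure manometer on the main tenderness point". Pressure from the Wagner FDK20 is applied slowly, after which the doctor "can measure the tenderness threshold and can remove the pain points below the tenderness threshold of 2 kg/cm" (unit kg/cm²). The located points are marked with a cross, and the section on the needling method then treats the selected points.

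Two other places bear on the meaning:

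- The secondary-outcome section on PPT and pressure pain tolerance (PTT) says that the measurement "will be performed using the FDK20 handheld pressure an algeometer manufactured by Wagner Instruments, USA". It defines the reading thus: "the data that will be transferred to the tester when the subject just felt pain, which will be recorded as PPT". On the unit it says: "The data will be analyzed in units of kg/cm" (again per square centimetre).
- The Discussion explains why the meter is used: "Based on the characteristics of MTrp with tenderness and referred pain", "we used a pain meter to determine the location of the local pain points in the shoulder joint".

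**The concern.** A pressure threshold runs opposite to tenderness: the sorer the point, the less pressure it takes to hurt. A rule that removes low readings therefore removes the sorest points. The experimental technique is meant to treat tender trigger points, so one would expect low readings to be kept.

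This sentence is the article's only numeric criterion for where the experimental needling goes. The authors themselves name the needling site as a key determinant of the effect of acupuncture. An operator who followed the sentence literally would leave the sorest candidates untreated, and a reader trying to reproduce the technique would not know which side of 2 kg/cm² to keep.

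**Working it through.** The article gives no power, sample size or error-rate figure on this point, so the check is one of direction.

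**1. Position of the sentence.** It stands after palpation and familiar-pain confirmation and before marking. In that place the plain meaning of *remove* is to drop a point from the set to be needled.

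**2. Scale of the reading.**

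| Feature | Group A point selection | PPT outcome |
|---|---|---|
| Device | Wagner FDK20 | Wagner FDK20 |
| Unit | kg/cm² | kg/cm² |
| Procedure | pressure applied slowly | pressure applied; reading taken when pain is first felt, then increased for PTT |
| Term used | tenderness threshold | pressure pain threshold |

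The first two rows match exactly and the third is compatible. The fourth differs, and the article nowhere defines the first term or states that it equals the second. Treating them as the same measurement is a well-supported inference, but still an inference.

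**3. Direction, given that inference.** With illustrative readings that are not in the article:

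- a point that hurts at 1 kg/cm²: 1 < 2, so it is removed;
- a point that hurts only at 3 kg/cm²: 3 > 2, so it is kept.

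The point that hurts at a third of the pressure is the one discarded. The literal rule keeps the less tender point and drops the more tender one.

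**4. Comparison with the Discussion.** There the points are described by their tenderness, and the meter is the instrument for finding them on that basis. A meter used for that purpose would be expected to retain low readings. The Discussion gives no cut-off, so the conflict is by implication. No section states the rule the other way round, and none gives a reason for excluding very tender points.

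**5. Reach.** The rule concerns group A only: 36 / 108 = 0.333, or 33.3% of planned patients (Sample size estimation). This is the size of the arm to which the rule applies, not a count of patients affected. That count would need the distribution of gauge readings, which is not given. The selection section does not say whether points are chosen afresh at each of the nine sessions, so no number of sessions can be attached either.

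**The case against.** The best defence is that this is a language problem in a translated text. *Remove* may stand for *pick out*, in which case the sentence already says the right thing. *Below the threshold* may mean *not tender enough*. The verb is also permissive, since the doctor *can* remove points. Context works against a literal misreading: the gauge goes on the main tender point, which has already reproduced the patient's usual pain, and discarding it for being tender would defeat the steps just taken. Only three acupuncturists deliver the treatment, each with at least five years' experience and training before the start. The pain tester is under SOPs, on which staff are trained. A condensed article may leave gauge handling to those SOPs.

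Much of this stands. A slip is the likeliest explanation, actual practice may well be correct, and points that are kept have still passed the palpation and familiar-pain screens. What does not stand is that nothing needs changing. The sections on training and SOPs do not state the direction, and the article is not silent on it: it gives a specific rule with a number. Permission to drop the sorest points still points the wrong way and leaves operators free to differ.

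A reader might infer more than the documents support:

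- *That the sponsor chose to avoid the most tender points.* Nothing shows such a choice.
- *That the article flatly contradicts itself.* The Discussion sets no cut-off and no ranking by tenderness. A point reading above 2 kg/cm² that reproduces the familiar pain is still tender.
- *That 36 patients are treated at the wrong sites.* No gauge readings are reported, and practice may follow the SOP rather than the sentence.

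**Conclusion.** The point holds as a correction to a stated rule. Read literally, and on the assumption that the tenderness threshold is read like the PPT, the sentence removes the most tender candidates from needling in the experimental arm. By implication this conflicts with the purpose that the Discussion gives for the meter. It is probably a slip of wording or translation.

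The consequence is limited to how the group A intervention is specified and whether it can be reproduced. Randomisation, sample size and error rates do not change. Whether 2 kg/cm² is a suitable cut-off cannot be judged from the document and is not questioned here. Confidence is medium, because the equivalence of the two terms is inferred and the SOP is not at hand.

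**What to change.** 1. Confirm the intended direction against the SOP and the training given to the three acupuncturists.
2. If low readings were meant to be kept, correct the sentence. For example: *Candidate points with a pressure pain threshold below 2 kg/cm² are retained and marked for needling.* Using the term PPT here would also settle the definition.
3. If excluding the most tender points is intended, say so and give the reason.
4. The first participant was enrolled on 02 Jan. 2020, so note which direction was applied to patients already enrolled, if this is known.

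A rule for a patient with no point below 2 kg/cm² would be a useful option, but it is not part of the correction.

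The cost is one reworded sentence, a check of existing material and a short note, with no new visit, measurement or device. Two reservations apply. The article does not say that selection readings or discarded points are recorded, so the note on past practice may rest on the operators' account. If the sponsor classes the change as an important modification, its own section on protocol amendments requires that the relevant parties be told, including the fund regulator, participants, registries and journals.

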#### The stuck-moving needle acupuncture method

The patient will take a seated position during acupuncture. After routine disinfection on the selected myofascial trigger points (MTrp), the skin will be cleaned with alcohol (75%). The applicator will tighten the patient’s skin with his or her left hand and will hold the stuck-moving needle (specification, 0.40 × 40 mm) in his or her right hand (the position of the needle is approximately 1 cm from the needle tip), and the stuck-moving needle will be inserted perpendicularly into the Trp (the degree of convulsions after the patient’s pain is triggered). Further, a needle will be twisted clockwise slowly (90–180°) until the muscle fibers are wounded and until the needle becomes tight and twisted. At this point, patient may describe pain and astringency. Then, the needle will be lifted again with 3 to 5 times by shaking. The strength of lifting the needle will depend on the patient’s condition and acupuncture position. Furthermore, a needle should be ejected quickly. While lifting the needle, the doctor will twist needle counter clockwise until the muscle fibers are relaxed. After the treatment, the patient will be supplemented with physical exercises. The exercise method is same as provided to group C.

##### Treatment course

One treatment every other day, three treatments per week, total of 9 treatments for 3 weeks.

### Group B: common acupuncture control group

#### Acupoints

Jianyu (LI15), Jianliao (TE 14), Jianzhen (SI 9), Biru (LI14), Ashi points.

#### Method of operation

The patient will be taken the lateral position and exposes the affected side of the shoulder. After routine sterilization of the acupuncture site, a milli needle with a diameter of 0.25 mm and a length of 40–50 mm will be used. The acupoint locations are based on the “2006 People’s Republic of China National Standard” (GB/T1234–2006), and the acupuncture operation is based on the textbook of the 12th Five-Year Plan of the Ministry of Health. The skin will be cleaned with alcohol (75%). Then, needle will be quickly pierced into acupoints with the depth of 1.9–2.6 in., and twirling the needle until “De qi”. After using the mild reinforcing-attenuating method, the needle is retained for 30 min. After daily acupuncture, exercise will be provided which is as same as group C.

#### Treatment

One treatment every other day, 3 times a week, 9 times for 3 weeks.

### Group C: physical exercise control group

The physical exercise method of the shoulder joint is carried out according to the physical exercise program recommended in the Evidence-based clinical guidelines for the diagnosis, “The Assessment and Physiotherapy Management of Contracted (frozen) Shoulder” prepared by Hanchard et al. [13] in 2012. The patient’s training will be consisted of 12 sports units, including active and passive training, for a total of 50 min. Each workout will have a professional physiotherapist ([name] physical therapist) to guide the treatment and provide a practical exercise program for the patient. Treatment will take place 3 times a week for 3 weeks for a total of 9 treatments. The basic movements are as follows: active shoulder joint exercise with bare hands, let the patient use the diseased shoulder joint as the axis of shoulder joint movement, and do small rotation movements of the shoulder joint. First, rotate clockwise for 4 min, then counterclockwise for 4 min. Subsequently, the intensity can be increased; the two movements alternated for a total of 20 min. In the later stage, strength of exercise will be increased with the help of the physiotherapist, and the passive movement will be carried out for 10 min. Then, it will be used for shoulder flexion, abduction, extension and internal rotation, external rotation, and other actions by means of assistive devices such as shoulder rotation training device and fitness ball technique. Finally, the standing training exercises will be carried out for the spine and side bends of the spine.

### Measures to improve patient adherence

On a voluntary basis with the signed informed consent, patient’s adherence will be improved using the subject manual and Short Messaging Service (SMS). The acupuncturists will possess at least 5 years of clinical experience in acupuncture practice. This is to ensure that the treatments will be administered consistently.

## Outcomes

The following outcomes will be assessed by independent outcome assessors. These assessors will be trained before participating in this trial and unaware of the group assignments. The outcome assessments will be performed at four time points including at the baseline, at the end of the stuck-moving needle acupuncture treatments, in the 4-week follow-up period, and at the end of the follow-up period.

### Main outcome indicators

The primary evaluation index in the trial will be the change involved in the scores on the Visual Analogue Scale (VAS) and measurement of range of joint motion (ROM) from the baseline period through the 12 weeks of the follow-up period.

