**Methods:**

Randomized controlled trial will be conducted in the three clinical centers of Qingyang Traditional Chinese Medicine Hospital, Qingyang Xifeng district People’s Hospital, and Qingyang Second People’s Hospital in China from February 2020 to January 2021. One hundred and eight frozen shoulder patients will be recruited and randomized into one of three groups in a 1:1:1 ratio of the stuck-moving needle acupuncture group, common acupuncture control group, and physical exercise control group. This trial will include a 1-week baseline period, a 3-week treatment period, and a 12-week follow-up period. During the 3 weeks of the treatment period, patients will receive nine sessions of acupuncture. The primary outcome will be related to change in the Visual Analogue Scale (VAS) and measurement of range of joint motion (ROM) from the baseline period to the 12-week follow-up period. Secondary outcome measures will include measurement of pressure pain threshold (PPT), pressure pain tolerance (PTT), Oxford Shoulder Score (OSS), 36-item short form survey, and patient satisfaction evaluation. Adverse events also will be recorded for safety assessment.

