#### Measurement of range of joint motion (ROM)

The degree of mobility of the shoulder joint was measured using the American muscle strength test and the joint mobility meter (portable) (Hoggan MicroFET3). This study will measure the angle of the shoulder flexion, extension, abduction, internal rotation, and external rotation.

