### Sample size estimation

According to the previous researches, the difference between the VAS score before and after treatment in the general acupuncture group was 4.7, with a standard deviation of 1, whereas the difference in VAS score before and after treatment in the functional exercise group was 3.5, with a standard deviation of 1 [14]. In combination with the pilot experimental results from this study, the VAS score before and after treatment of frozen shoulder patients with stuck-moving needle acupuncture dropped by 5.2 and the standard deviation was 1.06. This study was a prospective study with three groups and the sample size as 1:1:1. The sample size was calculated using *F*-test in software SAS 9.4, and we used single-factor analysis of variance to calculate the sample size. The test level was set at *α* = 0.05, β = 0.1, and the test efficiency was set at 1 − *β* = 0.9. The results showed that the test power was 0.931, and the number of samples in each group was not less than 30. By considering the problem of missing samples or losing to follow-up, the sample size will be increased by 20. This means that the minimum sample size of each group will be 36 patients, and finally, the total sample of the three groups will include cases not less than 108.

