### Statistical analysis

All statistical analysis will be carried out by the professionals using SPSS (v21.0) software. The participants in the statistical analysis will be unaware as well for the specific grouping content of the trial. This study will use a full analysis set (FAS) and per protocol set (PPS), and the final conclusion will be based on FAS. The full analysis set (FAS) is based on the intent to treatment (ITT). Patients who participate in randomization and receive at least one treatment will be included in the analysis. In the FAS analysis, for patients who do not complete the trial, the main indicators of the missing will be derived from the Last Observation Carried Forward (LOCF). Continuous variables will be presented as mean ± standard deviation (normally distributed data) or medians and ranges (non-normally distributed data). Frequencies and percentages will be used to count the data. All statistics will be performed by bilateral differential test, with *P* value < 0.05 considered statistically significant.

For the balance of basic values, analysis of variance or chi-square test or rank sum test will be used. For the primary and secondary outcome, the analysis of variance will be used. If confounding factors have an impact on the results, then the co-variance analysis will be used. For the safety analysis, the incidence of three groups of adverse events will be compared using a chi-square test, and the adverse events that will occur in this trial will be listed. At the same time, the paired *t* test will be used to compare the differences between the groups before and after treatment. The comparison among the three groups before and after treatment will be analyzed by variance. The rate changes before and after treatment in the three groups will be measured by chi-square test or non-parametric test.

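### The three-group ANOVA cannot show whether stuck-moving needling beats common acupuncture, and no rule says which primary result counts as success

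*Protocol article*

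**What the plan says.** - **Primary variables.** Main outcome indicators defines the primary index as the change in "scores on the Visual Analogue Scale (VAS) and measurement of range of joint motion (ROM) from the baseline period through the 12 weeks" of follow-up. The Discussion again lists VAS and ROM as primary.
- **Content of ROM.** "This study will measure the angle of the shoulder flexion, extension, abduction, internal rotation, and external rotation". No composite or lead angle is defined.
- **Time.** Outcomes schedules a baseline assessment and three later ones: "at the end of the stuck-moving needle acupuncture treatments, in the 4-week follow-up period, and at the end of the follow-up period". The abstract describes the primary change as running "from the baseline period to the 12-week follow-up period". Sample size estimation uses the change over treatment, for example "the difference between the VAS score before and after treatment in the general acupuncture group was 4.7".
- **Test.** Statistical analysis says: "For the primary and secondary outcome, the analysis of variance will be used". It sets two-sided P<0.05 for all tests. A paired t test is added for before against after treatment.
- **Question.** The abstract's discussion and the end of the section on the rationale for the intervention make A versus B the comparison of interest. The Discussion asks whether the new combination of needle and site is better than ordinary acupuncture at acupoints.

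**The concern.** A three-group F-test asks whether the three means are all equal. The plan's own figures put exercise (C) 1.2 points below B and 1.7 below A, while A and B differ by 0.5. The test can therefore be significant because of C alone, whatever the relation between A and B. The paired t test does not supply the missing comparison, because a before/after test works within a group.

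Separately, with more than one primary variable, one significance level and no statement of which results must be significant, the meaning of a positive trial is left open until the data are seen.

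At stake is the main conclusion: a significant primary ANOVA could be read as support for the new technique when it carries almost no information on that point.

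**Working it through.** **Inputs.** From Sample size estimation: mean VAS reduction 5.2 (SD 1.06) in A, 4.7 (SD 1) in B, 3.5 (SD 1) in C; 30 per arm, 36 with the loss allowance; α = 0.05. I use a common SD between 1 and 1.06. Correlations between primary variables are not given; I assume 0 to 0.9.

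**1. The plan's own power figure.** Power is the probability that a noncentral F with 2 and 3(n−1) degrees of freedom exceeds its 5% critical value, with λ = n·Σ(mean − grand mean)²/SD².
- Grand mean = (5.2 + 4.7 + 3.5)/3 = 4.467; sum of squares = 0.538 + 0.054 + 0.934 = 1.527.
- At n = 30, λ = 45.8 (SD 1) to 40.8 (SD 1.06), critical value 3.10, power above 0.999.
- The stated 0.931 at 30 per arm is not reproduced. Power is 0.921 at 10 per arm (SD 1) and 0.933 at 11 per arm (SD 1.03), so 0.931 fits about 30 patients in total. At 30 per arm it would need an SD of about 1.77.

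**2. A equal to B (4.7, 4.7, 3.5).** Grand mean 4.3; sum of squares 0.16 + 0.16 + 0.64 = 0.96. At n = 30, λ = 28.8 to 25.6 and the rejection probability is 0.998 to 0.996. At n = 36 it is above 0.999.

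**3. A worse than B by 0.5 (4.2, 4.7, 3.5).** Grand mean 4.133; sum of squares 0.004 + 0.321 + 0.401 = 0.727. At n = 30, λ = 21.8 to 19.4 and the rejection probability is 0.989 to 0.979.

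Across A better, equal or worse, the F-test is significant with probability at least 0.979.

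**4. The A–B contrast.** Two-sided t test, difference 0.5, noncentrality = 0.5/(SD·√(2/n)).

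| n per arm | Noncentrality (SD 1 to 1.06) | Power |
|---|---|---|
| 30 | 1.94 to 1.83 | 48% to 44% |
| 36 | 2.12 to 2.00 | 55% to 51% |

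For 90% power, 2(1.96 + 1.2816)²·SD²/0.5² gives 84.1 to 94.5, that is 85 to 95 per arm.

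**5. False-positive rate at one visit with no true effect, by success rule.**
- Any one of six (VAS and five angles): 1 − 0.95⁶ = 26.5% if independent. Simulated null ANOVAs (36 per arm, 10,000 runs) give 24%, 20%, 17% and 12% at correlation 0.3, 0.5, 0.7 and 0.9.
- Any one of two (VAS, and ROM as one variable): 1 − 0.95² = 9.75% if independent; simulated 7% at correlation 0.9.
- VAS and ROM both required: at most 5%.

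The article does not say which rule applies.

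**6. The visit.** A change score running from baseline through, or to, the 12-week follow-up most plainly means baseline to the last visit. The wording names a period that also contains the week-4 visit, and the planning figures are changes over treatment, so the text is loose and should be tied to one visit.

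**The case against.** **The aim is wider than A versus B.** The rationale for the design also compares both needling arms with exercise, and Study design speaks of three treatment options. An F-test is a reasonable first step for that. This stands, but a first step does not answer A versus B, and the article states no second step.

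**Alpha allocation and follow-up contrasts are often left to an analysis plan.** Partly right, and none is shown. The point rests on what the article itself fixes: two primary outcomes, one significance level for everything, and the three-group ANOVA as the test.

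**Six primary variables is an inference.** This stands. The article names two primaries and lists the angles measured; it does not say that each angle is a separate primary test. A reader might infer that the error rate is several times 5% as a matter of fact. The documents do not support that outright: it requires six separate variables and a rule that any one suffices, and neither is stated.

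**No primary visit.** A reader might also infer that all three post-baseline visits are open to selection. Six variables at three visits would give 25–54% (correlation between variables 0.9 to 0, between visits 0.6, both assumed). The texts do not support that reading, because they most plainly mean week 12, and the sample-size paragraph reports planning data without redefining the endpoint.

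**Misreporting is a prediction.** Correct: the plan nowhere says that a significant F-test will be presented as superiority of A.

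**Conclusion.** The firm part is the test. On the planning means and SDs, taken to hold at the primary visit, the F-test at 30 per arm rejects with probability 0.996–0.998 when A equals B and 0.979–0.989 when A is 0.5 points worse. The test as stated cannot answer the main question. This does not depend on how ROM is counted or on the exact visit.

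The inflation is conditional. It is about 12–27% at one visit for six variables and 7–10% for two, if any one significant result suffices, and absent if VAS and ROM are both required. The fault is that no rule is stated, so the error rate cannot be known. The loose time wording is a lesser matter. All of this should be settled before the data are analysed.

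**What to change.** 1. Name one primary endpoint: change in VAS from baseline to the 12-week follow-up visit. Treat end-of-treatment and week-4 results as supportive.
2. Test the three-group F at 0.05. Only if it is significant, test A–B, A–C and B–C, each at two-sided 0.05. With exactly three groups this is a closed procedure: if any two of the pairwise equalities hold, all three means are equal, and the F-test covers that case. Familywise error over the three VAS contrasts stays at 5%.
3. State that any claim of superiority over common acupuncture rests only on the A–B contrast, reported with its confidence interval.
4. Make the five ROM angles secondary, tested for A–B with Holm, and only if the VAS A–B contrast is significant. A significant F-test must not open this family. The sequence of A–B claims, VAS then ROM, is then held at 5%; say that this does not extend jointly to the comparisons with exercise.
5. Label the stated power of 0.931 as not applying to A versus B, and give the A–B power: about 51–55% at 36 per arm and 44–48% at 30, for the assumed 0.5-point difference.

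**Cost.** Changes to the outcome and analysis text and a registry update. ROM is no longer co-primary, although the Discussion gives a reason for choosing both outcomes. The plan must also admit that its key comparison is underpowered: 90% power would need 85–95 per arm, so a non-significant A–B result could not be read as equivalence.
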